### Protocol

This study will adopt a longitudinal design. Participants will be asked to visit the hospital at 2 time points; baseline (Time 1) and 6-month follow-up (Time 2). At each time point, participants will be asked to undertake 2 visits (i.e., visits 1 and 2) separated by a 7-day period. Specific protocols to be followed are described below.

#### Visit 1

Participants will visit the hospital to undertake physical assessments and complete questionnaires. At the end of Visit 1, participants will be fitted with the ActiGraph (GT3X) accelerometer and activPAL3^μTM^ posture sensor to wear for the subsequent 7 days. The researcher will give verbal and written instructions, plus a demonstration, regarding how to wear each device. Participants will also be given the Bouchard Physical Activity Record (BAR)^66^ to complete on 3 of the days during which they wear the GT3X and activPAL3^μTM^.

#### Visit 2

After 7 days, participants will re-visit the hospital to provide a fasted blood sample, and return the GT3X accelerometer, activPAL3^μTM^ posture sensor and BAR to the researcher. During this visit, they will also be asked to complete questionnaires with specific reference to their experiences of pain and fatigue over the previous 7 days.

### Measures

#### Visit 1

*Participant characteristics.* Information will be recorded pertaining to participants’ age, gender, ethnicity, marital status, education, date of diagnosis, existing chronic conditions (e.g., heart disease, diabetes, depression), current medical treatment, smoking status and living arrangements.

*Anthropometrics.* Taken in duplicate, height, weight and body composition will be measured with participants bare-foot, whilst wearing light and loose-fitting clothing. Height will be measured to the nearest 0.1cm using a stadiometer (SECA, Leicester Height Measure). Weight will be measured to the nearest 0.1kg using the Tanita Body Composition Scales (Tanita BC-418 MA P). Body Mass Index (BMI) will be calculated as weight (kg)/height^2^ (m^2^). Percent body fat and muscle mass will be measured using the Tanita Scales via bioelectrical impedance analysis.

*Resting blood pressure.* Resting blood pressure (systolic and diastolic) will be taken in duplicate with an automatic blood pressure machine (Mindray Accutorr PLUS). The blood pressure cuff will be placed over the brachial artery as standard, after the participant has rested in a supine position for 5 minutes.^36,67^

*Physical function.* Gait speed will be assessed using the 20-Metre Timed Walk Test to provide an objective measure of physical function. Participants’ time to walk from a ‘start line’ to a ‘finish line’, 20 metres apart, will be recorded using a stopwatch. The stopwatch will be started once the participant begins to walk from the ‘start line’, and will be stopped once the participant’s heel has completely crossed the ‘finish line’. Gait speed has been previously used in studies of RA to provide an objective measure of physical function (e.g., walking 15.24 metres).^68^ Research has also shown that slower gait speed is associated with RA outcomes, such as pain, fatigue and joint deformation.^69^ As such, it may also serve as a proxy for other important aspects of RA health, directly related to physical function.

*Questionnaires.* Validated questionnaires will be administered to the participant to assess self-reported RA outcomes and hypothesised determinants of SB and physical activity (see **Table 1**). Questionnaire scores will be calculated according to validated scoring instructions (e.g., mean scores will be calculated for the ‘autonomous motivation for reducing SB’ dimension in the Behavioural Regulation in Exercise Questionnaire-2).

**Table 1. T1:** Questionnaires administered at baseline (Time 1) and 6-month follow-up (Time 2), specifically on visit 1 to the hospital

**Outcome**	**Questionnaire**	**Description**	**Example**
Pain	McGill Pain Questionnaire	Questions pertaining to the past 2 weeks 17 items - Sensory descriptors - Affective descriptors - Present pain - Average pain	For each of these words, please place a tick in onecolumn: - E.g., Throbbing - (0 = none, to 3 = severe)
Fatigue	Multidimensional Assessment of Fatigue Scale	Questions pertaining to the past 2 weeks 16 items 4 dimensions: - E.g., Degree and severity Global fatigue index	Please complete the following items based on the past 2 weeks: - E.g., To what degree have you experienced fatigue? - (1 = not at all, to 10 = a great deal)
Fatigue	Multidimensional Fatigue Inventory	Questions pertaining to the past 2 weeks 20 items 5 dimensions: - E.g., Physical fatigue	Over the past 2 weeks: - E.g., I feel fit - (1 = yes that is true, to 5 = no that is not true)
Physical function	Health Assessment Questionnaire	Questions pertaining to the past 2 weeks 8 categories: Self-reported ability to complete activities of daily living - E.g., Dressing and Grooming	Are you able to: - E.g., Dress yourself, including tying shoelaces and doing buttons? - (0 = without any difficulty, to 3 = unable to do)
Physical function	Dartmouth Coop Functional Assessment Charts	Questions pertaining to the past 2 weeks 6 items 6 dimensions: - E.g., Physical fitness	During the past 2 weeks: - E.g., what was the hardest physical activity you could do for at least 2 minutes? - (1 = very heavy, to 5 = very light)
Sleep	Pittsburgh Sleep Quality Index	Questions pertaining to the past 2 weeks 18 items Aspects of sleep - E.g., Sleep disturbances Global sleep index	In the past 2 weeks: - E.g., How often have you had trouble sleeping because you have to get up to use the bathroom? - (0 = not during the past 2 weeks, to 3 = three or more times a week)
Satisfaction with life	Satisfaction With Life Scale	Questions pertaining to the present time 5 items Satisfaction with life	I currently feel: - E.g., In most ways, my life is close to my ideal - (1 = strongly disagree, to 7 = agree)
Vitality	Subjective Vitality Scale	Questions pertaining to the past 2 weeks 6 items Vitality	Over the past 2 weeks, generally: - E.g., I have been feeling alive and vital - (1 = not at all true, to 7 = very true)
Anxiety and depression	Hospital Anxiety and Depression Scale	Questions pertaining to the past 2 weeks 14 items Depression (7 items) Anxiety (7 items)	Over the past 2 weeks: - E.g., I still enjoy the things I used to enjoy - (0 = definitely as much, to 3 = not at all)
Positive and negative affect	Positive and Negative AffectSchedule	Questions pertaining to the past 2 weeks 20 items Words describing different feelings/emotions	Over the past 2 weeks: - E.g., Interested - (1 = very slightly or not at all, to 5 = extremely)
Quality of life	World Health Organisation Quality Of Life Scale	Questions pertaining to the past 2 weeks 26 items 4 domains: - E.g., Physical health	Thinking about the past 2 weeks: - E.g., How would you rate your quality of life? - (1 = very poor, to 5 = very good)
Support from participant-identified other for physical activity, reducing sedentary behaviour and breaking up sitting time	Important Other Climate Questionnaire	6 items - Perceived autonomy support from important other regarding physical activity, reducing sedentary behaviour and breaking up sitting time	With regards to being physically active/reducing my sedentary behaviour/breaking up my sitting time: - E.g., I feel that my important other provides me with choices and options about reducing my sedentary behaviour - (1 = strongly disagree, to 7 = strongly agree)
Support from consultant for physical activity, reducing sedentary behaviour and breaking up sitting time	Health Care Climate Questionnaire	6 items - Perceived autonomy support from consultant regarding physical activity, reducing sedentary behaviour and breaking up sitting time	With regards to being physically active/reducing my sedentary behaviour/breaking up my sitting time: - E.g., I feel that my consultant understands how I see things with respect to reducing my sedentary behaviour - (1 = strongly disagree, to 7 = strongly agree)
Need satisfaction for physical activity	Psychological Need Satisfaction For Exercise Scale	Questions pertaining to the past 4 weeks 18 items - Personal experiences of physical activity	With regards to my experiences of physical activity: - E.g., I feel free to do physical activity in my own way - (1 = false, to 6 = true)
Self-efficacy for physical activity and breaking up sitting time	Self-Efficacy for Exercise Scale	9 items - Extent of self-efficacy to take part in physical activity in different situations - Extent of self-efficacy to break up sitting time in different situations	How confident would you feel taking part in physical activity (e.g., walking) 3 times per week for 20 minutes if: - E.g., You felt pain when being physically active - (1 = not confident, to 10 = very confident) How confident would you feel breaking up your sitting time every 20 minutes if: - E.g., You did not enjoy breaking up your sitting time - (1 = not confident, to 10 = very confident)
Motivation for physical activity, reducing sedentary behaviour and breaking up sitting time	Behavioural Regulation in Exercise Questionnaire-2	Questions pertaining to the past 4 weeks 19 items - Reasons for taking part in physical activity, reducing sedentary behaviour and breaking up sitting time 5 dimensions: - Intrinsic regulation (autonomous motivation) - Identified regulation (autonomous motivation) - Introjected regulation (controlled motivation) - External regulation (controlled motivation) - Amotivation	I take part in physical activity/reduce my sedentary behaviour/break up my sitting time: - E.g., Because it is fun - E.g., Because I value the benefits of doing this - E.g., Because I feel guilty when I am not doing this - E.g., Because other people say I should - E.g., But I don’t see why I should
Motivation to limit screen time	Motivation to Limit Screen Time Questionnaire	Questions pertaining to the past 4 weeks 9 items - Feelings/beliefs regarding screen-time behaviour in leisure time	I try to limit my screen-time because: - E.g., I believe too much screen time is bad for my health - (1 = not true at all, to 7 = very true)
Environmental perceptions – active travel and physical activity	Assessing Levels of Physical Activity Scale	3 sections - Home and neighbourhood environment - Walkability	About how long would it take to get from your home to the nearest businesses or facilities listed below if you walked to them? - E.g., Supermarket - (1 = 1-5 min, to 5 = more than 30 min)

*Actigraph GT3X.* The GT3X triaxial accelerometer (27g; 3.8cm × 3.7cm × 1.8cm) will be attached to an adjustable elastic belt and worn on the right hip in a vertical position.^70–74^ Participants will be asked to remove the device only for sleeping and water-based activities (e.g., swimming, bathing), and to record all replacement/removal in wear time logbooks provided. The GT3X will record accelerations in 1-second epochs, which will be converted into activity counts. These counts will then be interpreted to determine the frequency, intensity and duration of SB and physical activity.

Data collected by the GT3X will be cleaned and analysed using Actilife Software (version 6). For inclusion in analyses, participants will be required to have worn the GT3X for ≥4 days, for ≥10 hours per day, including a weekend day.^25,75–78^ Non-wear (e.g., 60 minutes of ‘zero counts’) will be defined in accordance with previous research among older adults^75,78^ and people living with RA.^45^ Time spent in SB, LPA and MVPA will be determined using cut-points that have been validated in previous research with adults (e.g., Troiano et al.),^74^ and used in studies investigating SB and physical activity in the general population,^79^ in people with rheumatic diseases^80^ and in osteoarthritis.^81^

*ActivPAL3**^μTM^**.* The activPAL3^μTM^ posture sensor (9g; 2.35cm × 4.3cm × 0.5cm) will be initialised using activPAL3^μTM^ software and attached by the researcher to the front of the right thigh, in a mid-anterior position, with a waterproof, adhesive Tegaderm dressing. Participants will be asked to wear the activPAL3^μTM^ for 24 hours a day to enable assessment of time spent sitting/lying, standing and stepping, as well as sit-to-stand transitions.^82–85^ activPAL3^μTM^ software will be used to download the activPAL3^μTM^ data. Sleep time will be determined using self-reported information from the wear time logbooks and BAR, in conjunction with non-wear periods identified via algorithms applied to GT3X data. Specifically, the GT3X output generated by Actilife details at which time the participant removes (e.g., at bedtime) and replaces (e.g., at waking) the accelerometer throughout the 7-day period. This will be checked against the BAR, which details (over 3 days) when the participant woke up and went to bed.

Participants will be required to have worn the activPAL3^μTM^ for ≥4 days, for ≥10 hours per day, including a weekend day, to be included in analyses.^76,86–88^ Variables derived for analyses will include: time spent sitting/lying, standing and stepping (i.e., hours per day), as well as the number of sit-to-stand transitions (i.e., sedentary breaks per day).

*Bouchard Physical Activity Record.* Participants will be asked to self-report the dominant activity undertaken every 15 minutes, over 3 days of the study week, including a weekend day (e.g., Thursday, Friday and Saturday).^66,89,90^ They will be asked to report this information in real-time, in order provide information regarding the context in which SB and physical activity were undertaken. For this study, the BAR has been adapted to include visual analogue scales, in which participants will be asked to report their average, minimum and maximum pain and fatigue on each of the 3 days. Specifically, at the end of each day, participants will be asked to mark a vertical line along a 100mm continuum from ‘no pain/fatigue’ to ‘extreme pain/fatigue’.

#### Visit 2

*Fasted blood sample.* Blood will be taken from the inside of the arm and collected in appropriate vacutainers. Standard laboratory procedures and Enzyme-Linked Immunosorbent Assays (ELISAs) will be used to measure: serum biomarkers of inflammation (i.e., TNF-α, IL-6, high-sensitivity CRP, ESR), plasma lipids (i.e., total cholesterol, high-density lipoprotein cholesterol, low-density lipoprotein cholesterol, triglycerides), plasma glucose and insulin.

*Disease activity score-28*. The number of swollen and tender joints in 28 joints of the body (i.e., hands, wrists, elbows, shoulders and knees) will be examined. Tenderness will be assessed via participants’ self-report when light pressure is applied to the joint by the researcher. The degree of swelling will be visually assessed and self-reported by the researcher. The number of swollen and tender joints will be used in conjunction with patients’ ESR and a self-reported degree of overall health ranging from 0 (very good) to 100 (very poor), to determine patients’ disease activity score-28 (DAS-28).^91^

*Questionnaires.* Validated questionnaires will be administered to the participant on visit 2 to assess RA-related pain and fatigue during the study week (see **Table 2**). Questionnaire scores will be calculated according to validated scoring instructions (e.g., pain scores from the McGill Pain Questionnaire will be calculated by summing the intensity rank values for descriptors of sensory, affective and total pain).

**Table 2. T2:** Questionnaires administered at baseline (Time 1) and 6-month follow-up (Time 2), specifically on visit 2 to the hospital

**Outcome**	**Questionnaire**	**Description**	**Example**
Pain	McGill Pain Questionnaire	Questions pertaining to the past week 17 items - Sensory descriptors - Affective descriptors - Present pain - Average pain	For each of these words, please place a tick in one column: - E.g., Throbbing - (0 = none, to 3 = severe)
Fatigue	Multidimensional Assessment of Fatigue Scale	Questions pertaining to the past week 16 items 4 dimensions: - E.g., Degree and severity • Global fatigue index	Please complete the following items based on the past week: - E.g., To what degree have you experienced fatigue? - (1 = not at all, to 10 = a great deal)
Fatigue	Multidimensional Fatigue Inventory	Questions pertaining to the past week 20 items 5 dimensions: - E.g., Physical fatigue	Over the past week: - E.g., I feel fit - (1 = yes that is true, to 5 = no that is not true)

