### Aims of this research

This study will address the knowledge gaps and limitations of the existing literature, in order to build an evidence base regarding the health-related correlates of SB and LPA, and hypothesised determinants of these behaviours in RA.

The aims of this study are twofold:
To investigate the longitudinal relationships between objectively-assessed SB patterns (i.e., overall sedentary time, sedentary bouts and sedentary breaks) and LPA, with health outcomes in people living with RA. On the basis of evidence establishing an association between SB and inflammation in non-RA cohorts, we hypothesise that SB may contribute to disease outcomes in RA via perpetuating heightened systemic inflammation. As such, our primary health outcomes are: inflammatory biomarkers (e.g., Tumour Necrosis Factor-alpha [TNF-α], Interleukin 6 [IL-6], high-sensitivity C-Reactive Protein [CRP], Erythrocyte Sedimentation Rate [ESR]), which have previously been used as primary endpoints in non-RA studies examining the association between SB, inflammation and health.^14,15^ Secondary health outcomes are: broader disease-related outcomes (e.g., disease activity, CVD risk, pain, fatigue, physical function), indices of psychological wellbeing (e.g., depression, anxiety, vitality, satisfaction with life, positive and negative affect), and quality of life.To examine the longitudinal associations between hypothesised determinants (i.e., psychosocial [e.g., autonomy support], individual differences [e.g., self-efficacy] and physical environmental [e.g., home and neighbour-hood environment]) of SB and LPA (i.e., for: 1) reducing overall SB, 2) regularly breaking up SB and 3) physical activity), with objectively-assessed SB patterns (i.e., overall sedentary time, sedentary bouts and sedentary breaks) and LPA, in people living with RA.

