### Statistical Analyses

SPSS (version 24) will be used to compute descriptive statistics for all measured variables. These will include information regarding participant characteristics (e.g., gender, mean age, ethnicity), health outcomes (e.g., DAS-28, BMI), determinants (e.g., quality of motivation, self-efficacy), as well as levels of SB and LPA among the RA sample. Missing value analyses will be conducted via multiple imputation^92^ or expectation maximization^93^ methods in SPSS, where missing data does not exceed 5%.

Cross-sectional associations between RA participants’ objectively-assessed SB patterns and LPA, with health outcomes (Aim 1) and proposed determinants (Aim 2) will be examined using correlation and regression analyses. Longitudinal associations from baseline (Time 1) to 6-month follow-up (Time 2) will be analysed using regression models.

*Aim 1.* For cross-sectional analyses, objectively-assessed SB patterns and LPA will be independent variables. Dependent variables will include biomarkers of inflammation, disease activity, CVD risk, pain, fatigue, physical function, depression, anxiety, vitality, satisfaction with life, positive and negative affect, and quality of life. For longitudinal analyses, regression models will examine if changes in objectively-assessed SB patterns significantly predict change in health outcomes from baseline (Time 1) to 6-month follow-up (Time 2). Health outcomes will be examined in separate regression models, but analyses will be adjusted for other factors which may influence these associations, as appropriate (e.g., disease duration, age, gender, current medication, and GT3X and activPAL3^μTM^ wear time).

*Aim 2.* For cross-sectional analyses, the determinants of SB in RA (e.g., autonomy support and self-efficacy for physical activity, reducing SB and breaking up SB) will be independent variables, and objectively-assessed SB patterns and LPA in RA will be dependent variables. For longitudinal analyses, regression models will examine if changes in hypothesised determinants of SB and LPA (e.g., autonomy support for reducing SB) significantly predicts change in objectively-assessed SB patterns and LPA from baseline (Time 1) to 6-month follow-up (Time 2). As above, all analyses will be adjusted for potential confounders (e.g., 7-day pain and fatigue [to consider the possibility of bi-directional relationships], GT3X and activPAL3^μTM^ wear time).

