Subsequent analyses will use AMOS (version 24) to conduct path analyses and structural equation modelling, in order to examine multivariate relationships and hypothesised process models. For example, psychological processes (e.g., autonomy support for reducing SB) proposed to underlie objectively-assessed accumulated sedentary time and LPA engagement, in turn influencing RA disease outcomes (e.g., DAS-28) will be explored.^37,45,94,95^

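### The swollen joint count for the DAS-28 is described as a visual rating of degree; state that each joint is inspected and palpated and recorded as swollen yes or no

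*Protocol article*

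**What the plan says.** Everything on this point is in one paragraph of the protocol article (Measures, Visit 2, Disease activity score-28).

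- Joints and count: "The number of swollen and tender joints in 28 joints of the body (i.e., hands, wrists, elbows, shoulders and knees) will be examined".
- Tenderness: "Tenderness will be assessed via participants’ self-report when light pressure is applied to the joint by the researcher".
- Swelling: "The degree of swelling will be visually assessed and self-reported by the researcher".
- Use in the score: "The number of swollen and tender joints will be used in conjunction with patients’ ESR", together with the participant's own rating of overall health.

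Disease activity is listed among the secondary health outcomes (Aims of this research: "Secondary health outcomes are: broader disease-related outcomes (e.g., disease activity, CVD risk, pain, fatigue, physical function"). It is an Aim 1 dependent variable (Statistical Analyses: "Dependent variables will include biomarkers of inflammation, disease activity, CVD risk, pain, fatigue, physical function"), and the DAS-28 is the example outcome of the later path models ("in turn influencing RA disease outcomes (e.g., DAS-28) will be explored"). No other section describes how joints are examined for swelling.

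**The concern.** The paragraph sets out a procedure, and the procedure has three faults.

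1. **Method.** Touch is specified for tenderness and sight for swelling. A rule based on sight cannot count swelling that is palpable but not visible. It also gives the examiner no means of separating soft-tissue swelling from bony enlargement or deformity.
2. **Scale.** The rating is a degree, but the score takes a number of joints. No rule turns one into the other.
3. **Wording.** Self-report has no clear meaning for an examiner's rating, so two researchers could follow the sentence differently.

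At stake is the validity of one of the four DAS-28 inputs. Tenderness and overall health rest on the participant's report, and ESR is a laboratory value. The swollen count is the input that rests on the examiner's own judgement, and this sentence weakens it. Random error in the DAS-28 as a dependent variable lowers correlations and widens the intervals around regression slopes. Error that varied with sedentary time would also bias the slopes.

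**Working it through.** The plan gives no figure to reproduce. Its power calculations concern CRP, physical function, QRisk-2 and vitality, not the DAS-28. The check is therefore a comparison of the text, followed by an illustration.

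**Text, side by side**

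| Component | Method stated | What is recorded | What the score needs |
|---|---|---|---|
| Tender joints | Pressure by the researcher, participant's report | Tenderness at the joint | Number of tender joints |
| Swollen joints | Visual assessment | Degree of swelling | Number of swollen joints |

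The swollen row differs from the tender row in method, and what it records does not match what the score needs. The sentences before and after it both speak of a number, so a count is intended; the step from degree to count is not given.

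**Size, as illustration**

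Assumption: the swollen joints enter the DAS-28 as 0.28 × √S, where S is the number of swollen joints. The article does not print this weight. If a share f of truly swollen joints is missed, the score falls by 0.28 × [√S − √(S(1 − f))].

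| True S | f = 25% | f = 50% | f = 75% | f = 100% |
|---|---|---|---|---|
| 4 | 0.08 | 0.16 | 0.28 | 0.56 |
| 10 | 0.12 | 0.26 | 0.44 | 0.89 |

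For example, with S = 4 and f = 75%: 0.28 × (√4 − √1) = 0.28 × (2 − 1) = 0.28.

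Error can also run upward. If one deformed joint is counted as swollen in addition to 4 true ones: 0.28 × (√5 − √4) = 0.28 × 0.236 = 0.07. One joint missed and one wrongly counted leaves the score unchanged. Neither rate is in the article, so the net direction cannot be derived.

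**Cross-sectional and change analyses**

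If the same share f is missed at both times, the recorded term is √(1 − f) times the true term, and so is its change. The factor is √0.75 = 0.87, √0.50 = 0.71 or √0.25 = 0.50 for f = 25%, 50% or 75%. Take a true fall from 4 to 1 swollen joints with f = 50%:

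- True change: 0.28 × (1 − 2) = −0.28.
- Recorded change: 0.71 × −0.28 = −0.20.
- Error in the Time 1 level: 0.16. Error in the change: 0.08.

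A stable error therefore cancels in part. In the cross-sectional analyses, which the article also plans, the whole level error remains.

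**The case against.** The strongest case against is that this is loose wording in a condensed article. The text does not say that swelling is judged only by eye. The joints are said to be examined, the researcher has hands on them for tenderness, and the paragraph cites a source for the DAS-28. Examination technique is commonly left to a manual. A sentence that has a researcher self-reporting is weak evidence of a deliberate departure from the usual joint count.

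Part of this stands. That touch is excluded is an inference from the one method named, and joints may in practice be palpated. But the article does not leave the technique out: it states one. If the statement is wrong, it still needs correcting.

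Other limits also stand:

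- The examiner-judged component is degraded, not removed; the researcher still rates swelling.
- The primary outcomes are inflammatory biomarkers and do not depend on the joint count.
- Disease activity is one item in a list of examples of secondary outcomes, so its place in that list carries no weight.
- The weight of 0.28 and the miss rates are assumptions.

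A reader might go further and infer that disease activity will be understated. The article does not support this, because error can run both ways.

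A reader might also infer that the link between sedentary behaviour and disease activity will be distorted, because swelling is harder to see in people with more body fat or more joint damage, who may sit more. The article gives no data on either step. It names disease duration among its example adjustment factors and it measures body fat. This remains a possibility and not a finding.

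**Conclusion.** The point holds as a fault in a stated measurement procedure for a secondary outcome, and it should be corrected. As written, the swollen joint count rests on a visual rating of degree and is less valid than a count by inspection and palpation. The net direction and size of the resulting error in the DAS-28 are unknown. Under the assumed 0.28 × √S term, missing 25% to 100% of 4 swollen joints would lower a participant's score by about 0.08 to 0.56. The upper end needs every swollen joint to be missed and should not be read as the expected error. The cross-sectional DAS-28 analyses are the more exposed, the change analyses less so if technique and examiner are stable, and the primary biomarker analyses not at all. The conclusion that the text needs changing does not depend on the illustration: either the method is as stated and should be improved, or it is misdescribed and should be corrected.

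**What to change.** Replace the sentence on swelling with: *each of the 28 joints will be inspected and palpated by a researcher trained in the 28-joint count, at the same time as tenderness is tested, and recorded as swollen yes or no; the swollen joints are summed.* If this is already the practice, correct the article's wording to say so.

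The cost is one sentence and, if the researcher has not had it, brief joint-count training. No visit, assessor or equipment is added, because the researcher already presses on the joints.

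The downside arises if assessment has begun; the Discussion describes device use in the present tense, so it may have. Changing technique between Time 1 and Time 2 would create apparent change. With 4 swollen joints at both times, half of them missed by eye at Time 1 and none missed at Time 2, the score would rise by 0.16 with no change in disease. Participants already assessed by eye at Time 1 should therefore have the same technique at Time 2, or both techniques recorded at Time 2, and the technique used should be noted in the data.

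### ESR is both a primary inflammatory outcome and a component of the DAS-28, so any test of the inflammation-to-disease-activity route that pairs the two is partly true by construction

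*Protocol article*

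**What the plan says.** Four statements in the protocol article bear on this point.

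- **Aims of this research, outcome hierarchy.** The text says "our primary health outcomes are: inflammatory biomarkers", and ESR is named in that list beside TNF-α, IL-6 and high-sensitivity CRP. Disease activity stands on the next tier: "Secondary health outcomes are: broader disease-related outcomes (e.g., disease activity, CVD risk, pain, fatigue, physical function".
- **Aims of this research, mechanism.** The reason given for that choice is that "we hypothesise that SB may contribute to disease outcomes in RA via perpetuating heightened systemic inflammation".
- **Measures, Visit 2.** ESR is one of the inflammatory biomarkers measured at this visit. The DAS-28 is then formed at the same visit: "The number of swollen and tender joints will be used in conjunction with patients’ ESR", together with the patient's own rating of overall health. No second ESR measurement is described.
- **Statistical Analyses.** Each health outcome has its own regression model. Path analysis and structural equation models follow; in the example given, psychological processes act on sedentary time and light activity, "in turn influencing RA disease outcomes (e.g., DAS-28) will be explored".

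The article does not mention that ESR sits on both sides of the inflammation and disease-activity divide. It names no ESR-free version of the score and no component-level analysis.

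**The concern.** A composite that contains a variable correlates with that variable whatever its other components do. Here the shared variable is a primary outcome, the composite is a secondary outcome, and the stated mechanism runs from the first to the second. Two readings of the results are exposed.

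1. In a process model with ESR as mediator and DAS-28 as endpoint, the mediator-to-endpoint leg is inflated by the shared term, and the error runs in favour of the study's own hypothesis.
2. If both the SB-ESR and the SB-DAS-28 regressions are positive, the second may be read as corroborating the first, although part of it is the same measurement counted again.

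At stake is whether the study can tell that inflammation relates to joint disease and patient-rated health, or only that ESR relates to a score containing ESR.

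**Working it through.** **Inputs from the article.** The four DAS-28 components (Measures, Visit 2); ESR as a primary outcome (Aims of this research); n = 125, power 0.80, α = 0.05 (Power Calculation).

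**Inputs assumed.** The share s of DAS-28 variance supplied by the ESR term is not given; 5% to 50% is used. The correlation of the other biomarkers with ESR is not given; 0.3 to 0.7 is used. ESR is taken on the scale on which it enters the score.

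**The article's own figure.** The sample size cannot be reproduced, because no effect size or sidedness is stated. It can be back-solved with Fisher's z:

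- two-sided: r = tanh((1.960 + 0.842)/√122) = 0.248
- one-sided: r = tanh((1.645 + 0.842)/√122) = 0.221

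The point does not depend on this figure. It sets n, and a plausible SB-ESR correlation, for the illustration.

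**Step 1: the part-whole correlation.** Write DAS-28 = E + R, where E is the ESR term and R the remainder, unrelated to E. Then corr(E, DAS-28) = √s. The chance that this correlation is significant at n = 125 is Φ(atanh(√s)·√122 − 1.96). For s = 5%: atanh(0.224) × 11.05 − 1.96 ≈ 0.55, so Φ = 0.71.

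**Step 2: the indirect effect.** SB → ESR → DAS-28 was simulated with 4,000 runs per value of s, n = 125, an SB-ESR correlation of 0.248, and R unrelated to SB and ESR. The indirect effect counts as significant when both legs are.

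| s | corr(ESR, DAS-28) = √s | P(significant), Fisher z | ESR → DAS-28 leg significant, simulated | Indirect effect significant, simulated |
|---|---|---|---|---|
| 5% | 0.22 | 0.71 | 69% | 55% |
| 10% | 0.32 | 0.95 | 95% | 76% |
| 20% | 0.45 | about 1.00 | about 100% | 81% |
| 30% | 0.55 | about 1.00 | 100% | 80% |
| 50% | 0.71 | about 1.00 | 100% | 81% |

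The ceiling near 80% is the power of the SB → ESR leg. With E removed from the score, the ESR correlation is 0 under the same assumptions and P(significant) is 0.05.

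**Step 3: other biomarkers.** For a marker correlated c with ESR and otherwise unrelated to the score, the induced correlation is c·√s. At s = 20% this is 0.13 for c = 0.3, 0.22 for c = 0.5 and 0.31 for c = 0.7.

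**Step 4: carry-over into the SB-DAS-28 regression.** The induced correlation is 0.248 × √s. For ESR-DAS-28 correlations of 0.44 to 0.64 (s of about 19% to 41%):

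- 0.248 × 0.44 = 0.11, significant in about 23% of studies of 125
- 0.248 × 0.64 = 0.16, significant in about 42%

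**The case against.** The strongest reply is that the criticised model is not written down. The example in Statistical Analyses runs from autonomy support through sedentary time and light activity to DAS-28, with no inflammatory mediator. In the Aim 1 regressions, biomarkers and disease activity are both dependent variables, and inflammation never predicts DAS-28. The mechanism sentence serves to justify the choice of primary outcomes. This stands: a reader might infer that the article specifies an ESR-to-DAS-28 path, and it does not. The arrow follows from combining the stated hypothesis with the plan to fit process models whose example endpoint is DAS-28. The point is therefore conditional on that pairing.

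Three further objections also stand.

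- A reader might infer that the overlap alone creates an indirect effect. It does not: without a real SB-ESR association there is none.
- A reader might infer that the SB-DAS-28 regression is biased. It estimates the association with DAS-28 as defined, and ESR belongs to that definition. The carry-over in Step 4 is modest and would usually miss significance.
- The sizes rest on assumed shares and correlations, and they are cross-sectional. For the planned change-on-change models the algebra is the same, with s the ESR share of variance in DAS-28 change, but that share is also unknown.

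The objection that model content may be left to a fuller document carries less weight. The outcome tiers, the composition of the score, the mechanism and the example endpoint are all fixed in the article, and the overlap follows from them.

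**Conclusion.** The point holds in conditional form. If the inflammation route is tested with ESR against DAS-28, the second leg is partly ESR predicting itself. Its correlation is 0.22 to 0.71 for an assumed ESR share of 5% to 50%, even when ESR is unrelated to joint counts and patient-rated health. With an SB-ESR correlation of 0.248 and n = 125, the indirect effect would then be significant in about 55% to 81% of studies. That the coupling exists follows from how the score is defined; its size depends on the assumptions.

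It applies in full to ESR only. For TNF-α, IL-6 and high-sensitivity CRP it arises solely through their correlation with ESR and is weaker. It would also go too far to conclude that ESR and DAS-28 are not separate evidence at all: three of the four components are not ESR, so the two results are separate but not fully independent.

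**What to change.** Keep DAS-28 as the disease-activity outcome and state that it contains ESR, which is also a primary outcome. Then:

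- In any path or mediation model that pairs an inflammatory marker with disease activity, use the ESR-free components already collected (swollen count, tender count, patient-rated overall health), or a score without the ESR term, as the endpoint or as a required sensitivity analysis.
- If the SB-ESR and SB-DAS-28 results are to be read together as corroboration, report the same ESR-free analysis beside the SB-DAS-28 regression.
- Do not replace ESR with high-sensitivity CRP in the score for this purpose. It is also a primary outcome, so the problem would only move.

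The cost is a few extra models on existing data, with no new visits or assays. The ESR-free components have no standard disease-activity cut-offs, which is why DAS-28 stays for description. Fixing one ESR-free analysis in advance limits the added number of tests.
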